### Randomization of Practices Design Issues and Potential Bias

All practices consenting to participate in this trial will be randomized, stratified for urban (Edmonton/Calgary) versus nonurban and academic (trainees routinely evaluate patients) versus nonacademic practices. A statistician not aware of our project question will allocate practices using a standard randomization software. We have chosen practices as the unit of randomization because most individual practitioners within a shared practice use the same EMR and we wish to prevent contamination. Because we are testing the effectiveness of embedding the pathway into clinicians’ EMR and train-the-trainer CDM professional education, consenting practices randomized to usual care will not have access to either intervention, and therefore the risk of significant contamination is small. In addition, the design provides an opportunity to test for contamination by comparing the difference between the pre- and post-periods for the 2 groups (ie, intervention and control).

Practices will be randomized to either:

Routine care versus interventionEmbedding a primary care clinical pathway for managing childhood asthma into clinicians’ EMR to facilitate practitioners utilizing best evidence, and training these practices’ CDM professionals to provide asthma education to children with asthma and their parents.

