Even if children are prescribed appropriate medications, parents frequently do not receive adequate information and education to understand the rationale and importance of using preventive medications, which often results in poor adherence [35-37]. *Adherence* refers to a patient successfully taking medication. *Primary adherence* refers to the obtaining of medication prescribed, and *secondary adherence* refers to proper completion of the regime as intended by the prescriber. A World Health Organization [38] review indicated 30% adherence to medications by children and adolescents with asthma, which is among the lowest reported for any chronic disease. There is good evidence, however, that asthma education programs for children with severe exacerbations requiring emergency department and in-hospital care sufficiently improve adherence to reduce subsequent hospitalizations, emergency department visits, and urgent disease-related physician visits by 20-30% [39].

We propose to improve the prescription and use of evidenced-based preventative therapies for children with asthma, with the goal to significantly improve their disease control and quality of life, and reduce unnecessary emergency department visits and hospitalizations by 20% each. We will achieve this by (1) installing a primary care clinical pathway for managing childhood asthma into clinicians’ electronic medical record (EMR) to facilitate the use of best evidence by practitioners, and (2) training chronic disease management (CDM) health professionals to provide targeted and timely asthma education to parents and children with asthma. We will test this pathway and education project in a representative sample of 22 Alberta primary care practices, using a pragmatic cluster-controlled trial methodology. Specifically, we will determine if our proposed innovation, as compared with usual care,...

...increases *prescription* of evidenced-based preventative therapies;...increases *dispensing* (primary adherence) of evidenced-based preventative therapies;...improves children’s *asthma control*;...improves *quality of life* for children and families; and...decreases *health care utilization* (emergent primary care visits, emergency department visits, and hospitalizations) for asthma, and decreases overall societal (health system and family) costs.

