### Foundational Activities

In Spring 2011, the *AHS* Respiratory Network—now formally known as the “Respiratory Health Strategic Clinical Network (RHSCN)”*—*adopted the childhood asthma pathway initiative, in collaboration with the *AHS* child health community, as one of its 3 top priorities and provided human and financial resources to move the pathway initiative forward. The initial project of the *RHSCN* and our project team was to develop, implement, and evaluate emergency department and in-patient pathways, for which we received the *Canadian Institutes of Health Research Partnerships for Health System Improvement* funding. Concurrently, with the start of the emergency department/in-patient pilot project and the ongoing implementation of the emergency department and in-patient pathways across the province, the *RHSCN* started developing the primary care pathway.

In Fall 2013, our team developed a collaboration with the *Health Quality Council of Alberta (HQCA)* who have agreed to extract, link, and analyze health administrative data (which they routinely receive and utilize) and other data provided to them from 2 Albertan community-based primary care research networks (Northern and Southern Alberta Primary Care Research Networks—*NAPCReN* [40] and *SAPCReN*, respectively 41). These networks are regional networks contributing to the *Canadian Primary Care Sentinel Surveillance Network* (*CPCSSN*) [42]. *CPCSSN* extracts clinical data quarterly from participating practitioners’ (*sentinels*) EMRs, cleans them, removes identifiers, and makes these data available for surveillance, epidemiology, and health services research. With the principal investigator [name], *CPCSSN* is currently developing and validating a case definition and case finding algorithm for childhood asthma, which will be added in due course to its routine data extraction and processing. The networks contributing to *CPCSSN* in Alberta are currently able to process data from both the *Wolf* and *Med Access* EMR systems. These networks have agreed to assist with recruiting practices to participate in this project.

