## Methods

### Project Objectives

We propose a 3-year mixed-methods health services research project using a randomized cluster-controlled trial design (with primary care practices as the cluster; trial registration number NCT02481037) to achieve the following objectives:

To use the Theoretical Domains Framework (TDF) to refine our implementation strategy;To implement the intervention (a childhood asthma primary care clinical pathway in EMRs and identifying and training CDM health professionals to provide asthma education) in the 11 practices in the intervention arm;To evaluate our project intervention using interviews, health administrative and EMR databases, and child and parent surveys of quality of life, the child’s asthma control, and the socioeconomic burden of the child’s disease on their family; andTo develop a detailed “scale and spread” strategy if our intervention is shown to be successful (ie, yields either cost savings or improved child and parent quality of life) for all Alberta primary care practices who use a supported EMR.

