### Project Population

Practices will be recruited from those who are currently or are becoming a member of the *NAPCReN* or *SAPCReN.* All children (1-17 years of age at the time of enrollment) who meet the case definition of asthma (and are seen by a participating primary care practitioner within a consenting practice) will be included in the trial’s analysis unless they refuse consent [53]. The *CPCSSNs* use a “social contract” consent process, where practice populations are informed generally about research, information is freely available on specific projects, and people are included unless they object [53]. Because the project will collect data outside the *CPCSSN* protocol, parents of children with asthma in the participating practices will be sent a letter by their primary practitioner outlining implied consent and asking them to complete surveys about quality of life, asthma control, and the burden (impact) of asthma on their family.

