### Sample Size Calculation and Analysis

Our *AHS* partners provided the number of pediatric asthma incidences billed by each practice in the province. We will use this information to select practices that have more than 70 active, eligible asthma patients. In addition, the Primary Care Asthma Working Group of clinicians agreed the minimal clinically important difference to be 20% (see Multimedia Appendix 1 for a detailed sample size calculation).

Patients included in the analysis of the primary and one of the secondary outcomes (proportion of children dispensed a preventive medication) will be categorized as either “successful” or “not successful” based on the logic outlined in Multimedia Appendix 2. Given the clustered nature of patients’ “success” within practices, a mixed effects logistic regression model will be performed where clustering is considered. Odds ratios for success between arms will be presented along with 95% CIs. The modeling will include assessment of potential confounders and independent risk factors. To analyze the other secondary outcomes (quality of life and asthma control and emergency department visits/hospitalizations), we will use a linear mixed effects regression model, and include fixed effects for the baseline/follow-up periods, the pathway/control arms, and stratifications/interaction, and random effects to account for clustering in practices.

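### With 22 practices the arms may start apart on preventer prescribing by chance, and the stated primary model names neither the practice's baseline rate nor the stratification factors

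*Protocol article*

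**What the plan says.** The Background and Overview section of the protocol article sets the number of practices: "We will test this pathway and education project in a representative sample of 22 Alberta primary care practices". Project Objectives places the intervention "in the 11 practices in the intervention arm", which implies 11 controls. The randomisation section makes allocation "stratified for urban (Edmonton/Calgary) versus nonurban and academic (trainees routinely evaluate patients) versus nonacademic practices" and adds "A statistician not aware of our project question will allocate practices using a standard randomization software". No balancing on earlier prescribing or practice size is described.

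Information on both exists. Under Sample Size Calculation and Analysis, the health service "partners provided the number of pediatric asthma incidences billed by each practice in the province", but the counts serve only as an eligibility floor: "We will use this information to select practices that have more than 70 active, eligible asthma patients". The surveillance network "extracts clinical data quarterly from participating practitioners", and those records include prescriptions. The Primary Outcome section calculates the preventer proportion separately for a baseline and a follow-up period.

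For the primary outcome and the dispensing outcome, the analysis is a mixed effects logistic regression that allows for clustering and reports an odds ratio between arms. Potential confounders and independent risk factors are to be assessed, but none is named. Fixed effects for period, arm and stratification are listed only for the linear mixed model used for the remaining secondary outcomes.

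**The concern.** Two binary factors make four cells, on average 22/4 = 5.5 practices each. That controls location and teaching status but leaves each practice's prescribing habit largely to chance. The outcome is itself a prescribing proportion, so a practice's earlier value is likely to be the best single predictor of its later one.

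A starting gap between arms passes partly into the follow-up comparison. A 5-point gap is a quarter of a 20-point difference. It is half of the difference if the article's 20% is relative (50% v 60%); the text does not say which is meant. At stake are precision and how convincing the odds ratio looks. An open-ended confounder assessment also leaves room for the adjustment to be chosen after the imbalance has been seen.

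**Working it through.** **No figure to reproduce.** The derivation of 22 practices is in Multimedia Appendix 1, which is not shown. The article gives no ICC, so the ICC is varied below.

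**Inputs from the article.** 11 practices per arm; more than 70 eligible children per practice, taken as m = 70; baseline preventer rate p = 0.50, from the Alberta pharmacy figure in the Introduction.

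**Assumed.** ICC 0.02, 0.05 or 0.10; correlation ρ = 0.7 or 0.9 between a practice's true baseline and follow-up rates; equal practice sizes; strata unrelated to the rate.

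**Step 1: chance gap in true starting rates.** SD = √[p(1−p) × ICC × 2/11], with normal tails.

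| ICC | SD (points) | Gap ≥ 5 points | Gap ≥ 10 points |
|---|---|---|---|
| 0.02 | √(0.25×0.02×2/11) = 3.0 | 10% | 0.1% |
| 0.05 | √(0.25×0.05×2/11) = 4.8 | 29% | 4% |
| 0.10 | √(0.25×0.10×2/11) = 6.7 | 46% | 14% |

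Simulation of stratified allocation with assumed cells of 9, 6, 5 and 2 practices agrees with these figures. If the strata explained 30% of the between-practice variance, the gaps would be somewhat smaller.

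**Step 2: SD of the follow-up arm difference without baseline adjustment.** Sampling of children is now included: SD = √[0.25 × (ICC + (1−ICC)/70) × 2/11]. This gives 0.039, 0.054 and 0.072.

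**Step 3: the same with adjustment for the practice's observed baseline rate.** The observed correlation is r = ρ × ICC/(ICC + (1−ICC)/70). The SD is multiplied by √[(1−r²)(1 + 1/18)], where 1/18 is the price of estimating one slope from 22 practices.

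| ICC | r at ρ = 0.7, 0.9 | Adjusted SD | Reduction |
|---|---|---|---|
| 0.02 | 0.41, 0.53 | 0.037, 0.034 | 6%, 13% |
| 0.05 | 0.55, 0.71 | 0.046, 0.039 | 14%, 27% |
| 0.10 | 0.62, 0.80 | 0.058, 0.044 | 19%, 38% |

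A simulation that also put the two stratification factors in the model gave reductions of 6 to 13%, 14 to 27% and 19 to 37%. The two extra terms cost almost nothing.

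**Step 4: sensitivity to denominator.** Only children prescribed a reliever count in the outcome, so the denominator may be well below the number of asthma patients. With m = 35 the same formulas give reductions of 2 to 5%, 8 to 17% and 15 to 28%.

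**Step 5: what constrained allocation would add.** Drawing from the best-balanced 10% of stratified allocations cuts the SD of the true starting gap from 0.048 to 0.023 (ICC 0.05) and from 0.069 to 0.024 (ICC 0.10). Once the analysis adjusts for baseline, the SD of the estimated effect barely moves. Stratified v constrained, it is 0.045 v 0.045 and 0.038 v 0.039 at ICC 0.05 (ρ = 0.7 and 0.9), and 0.057 v 0.055 and 0.045 v 0.043 at ICC 0.10. That is a gain of about 0 to 5%.

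All of this is on the risk-difference scale at practice level, as an approximation to the logistic mixed model.

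**The case against.** Stratified allocation by an independent statistician is valid. Any imbalance it leaves is part of the between-practice variance that a clustered confidence interval already carries. That stands in full. A reader might infer that the comparison is biased or the randomisation faulty, and the article gives no ground for either.

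A reader might also infer that allocation had to be constrained on prescribing rate. Three facts weigh against that. The asthma case definition, which sets the denominator, was still being developed and validated. Practices are drawn from those already in the networks or still joining: "Practices will be recruited from those who are currently or are becoming a member of the", so earlier extracts cannot be assumed for all of them. And step 5 shows that adjustment secures nearly all of the gain without holding up allocation, in a project that recruits from September 2015 and ends in March 2018.

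Nor can it be said that the scheme will miss 11 per arm. That depends on cell sizes and blocking, which the article does not give; cells of 8, 6, 4 and 4 with even splits always give 11:11.

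Finally, covariate lists normally belong in an analysis plan, and one may exist that settles this. The objection has force, and it keeps the point minor. What remains is that the article does describe the primary model, and describes it less fully than the model for other secondary outcomes. The pre/post comparison in the randomisation section is offered as a check for contamination, not as the primary estimator.

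**Conclusion.** The point holds as a low-severity improvement to the primary analysis. The chance gap in starting preventer rate has an SD of about 3 points at ICC 0.02, 5 at 0.05 and 7 at 0.10. The primary model as stated does not commit to using the baseline rate that the trial will calculate anyway, nor the factors on which it stratifies.

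Committing to them would lower the SD of the arm difference by about 15 to 40% at ICC 0.05 to 0.10 and by about 6 to 13% at ICC 0.02, given m = 70 and ρ of 0.7 to 0.9. With smaller denominators or a lower correlation the gain shrinks; at ICC 0.02 and m = 35 it is only 2 to 5%. The ICC and ρ are assumptions, not figures from the article. The size of the gain is therefore uncertain, although its direction is not in doubt over the range examined.

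**What to change.** Prespecify, in place of an open confounder assessment, that the primary mixed effects logistic model includes the practice's baseline-period preventer proportion, urban/nonurban status and academic/nonacademic status as fixed covariates. Calculate the baseline proportion with the same numerator and denominator rules as at follow-up. Do the same for the dispensing outcome with its own baseline proportion. The data are already to be collected. With an intercept, arm and three covariates, 22 − 5 = 17 practice-level degrees of freedom remain. The cost is a sentence in the analysis plan, fixed before follow-up data are seen.

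Optionally, if practices are still to be allocated in batches, constrain allocation within the existing strata on asthma volume, which is already held, and on a provisional baseline rate where extracts exist. Any constraining variable should then also be in the model. This gives better visible balance but little further precision. It needs a short program and may delay allocation while a batch consents and is extracted.

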### Quantitative Data

Data will come from 3 sources, namely, health administrative sets, data extracted from participating practices’ EMR, and surveys of asthma control, quality of life, and socioeconomic factors. Health administrative datasets will include Alberta Patient Registry, emergency department visits (*National Ambulatory Care Reporting System*), hospitalization abstracts (*Discharge Abstract Database*), practitioners visits (*Alberta physician/NP claims*), and pharmacy dispensing (*Pharmaceutical Information Network*); these datasets are considered to be of good quality with accurate personal identifiers on more than 95% of records. As previously noted, EMR data using a validated case definition will be extracted for all children with asthma meeting the inclusion/exclusion criteria. This will provide individual categorical and continuous patient-level data such as patient demographics, encounter history, medication prescriptions, and comorbid disease. Also as previously noted, the *HQCA* will play a pivotal role in our trial as they will (1) receive the aforementioned datasets from *AHS*, Alberta Health, and *NAPCReN/SAPCReN*; (2) extract and link the necessary data using a separate file from the practitioners, which will contain patients’ *CPCSSN* identifier linked to their Alberta Health Care Number; (3) perform the planned analysis; and (4) provide the aggregated results to our research team.

Letters from participating practitioners will be sent two times to families of children with asthma before and 11 months after the study intervention starts. The letter will inform parents about the purpose of the survey (though the broad purpose of the project will not be revealed to maintain masking) and will ask the primary parent or caretaker to go online to review the information sheet and complete a socioeconomic survey and the *Paediatric Asthma Caregiver’s Quality of Life Questionnaire (PACQLQ)* for children with asthma, or to complete written copies of the questionnaires and return them by self-addressed stamped envelopes. A previous study [54] has validated the *PACQLQ* for use by parents of children less than 7 years of age. Children 7 years and older will be asked to also complete the *Standardised Paediatric Asthma Quality of Life Questionnaire* and the *Asthma Control Questionnaire* [55]. The socioeconomic survey includes questions such as day care or school days missed, parent work days missed, and asthma medications purchased in the last 30 days, to allow calculation of the economic impact of a child’s asthma on their family.

### Qualitative Data

We will purposefully select 6 practices randomized to the pathway and education intervention based on size of the practice and heterogeneity of professionals in the practice [56], and evaluate them using multidisciplinary focus groups after the intervention. The interview protocols will be developed following the implementation of the intervention to incorporate key learning from the implementation into the question development. The focus groups will include practitioners and other professionals, for a total of at least six clinicians, and will be recorded by a court reporter [57]. The content of the interview questions will be guided by the Knowledge to Action Model [58] and will target areas such as attributes of the pathway, adopters, and implementation setting. Clinicians will have the opportunity to provide feedback regarding potential challenges with the pathway and offer suggestions for improvements.

To monitor the progress and permit follow-up of ideas that emerge from the focus group, data collection and analysis will follow an iterative and concurrent process. The post-implementation focus group data will be analyzed in the following three phases: coding, categorizing, and developing themes [59]. First, data for each practice will be coded to facilitate analysis. The code word(s) will reflect the essence of the data leading to ease of recognition as the number of code words increases. Codes will be operationally defined so that they can be consistently applied throughout the data. Second, codes will be placed into broad categories that correspond to the major unit of analysis. As categories emerge, their theoretical properties will be defined. Third, comparisons between categories will be carried out to locate similarities and differences among them. Data analysis will be carried out using NVivo 10.

### Economic Analysis

The potential for provincial-wide savings is achievable because of the high-quality evidence (numerous randomized controlled trials, systematic reviews, and international consensus guidelines) demonstrating that appropriately tailored anti-inflammatory medications reduce emergency department visits and hospitalizations and that asthma education training targeted to focus on families with children with more severe disease also yields a 20% reduction in subsequent hospitalizations, a 30% reduction in emergency department visits, and a 30% reduction in nonscheduled urgent physician visits for disease exacerbation [39]. Further validating the ability of preventative therapy for asthma to reduce health care utilizations and costs, health services studies in children and adults in both British Columbia and Sweden utilizing administrative data have shown that higher utilization of inhaled corticosteroids is correlated with lower rates of hospitalization and lower overall health care costs [60,61].

The primary analysis will be from the health care system perspective. Total health system costs per child with asthma in the 2 trial arms before and after the intervention will be determined. Health system costs will be disaggregated into the following three parts: (1) those stemming from pathway implementation and train-the-trainer education sessions, 2) those from asthma education provided by CDM professionals, and (3) those from hospitalizations and emergency department and practitioner visits for asthma. Overall health system costs will be considered decreased by the project intervention if the cost decrease from reduced emergent physician visits, emergency department visits, and hospitalization outweighs the cost increase from pathway implementation and asthma education. The impact on costs will be considered alongside the impact on outcomes including quality of life. A secondary analysis will also include consideration of family costs that consist of parent loss of work, travel, or other out-of-pocket costs due the child’s disease.

Costs stemming from health care utilization (drugs, hospitalizations, emergency department, and practitioner visits) will be derived from health administrative data. Actual costs are available from *AHS* for in-patient stays at Calgary and Edmonton Zone hospitals, and costs for other Alberta hospitals can be approximated using Institute of Health Economics (IHE) provincial estimates [62]. Emergency department visit costs will be determined using the IHE standard provincial estimates [62]. Surveys of staff and parents of children with asthma from each of the participating practices will provide cost estimates by collecting the following data: time spent on train-the-trainer sessions, staff time to educate families, and family quality of life measures, as well as out-of-pocket expenditures on their child’s disease.

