#### Development of EMR Embedded Pathway

The EMR prototype (developed in *Med Access* and currently being developed in *Wolf*) provides practitioners with dropdown menus to document key findings from medical history review and physical examination, classify patient’s disease phenotype to generate therapeutic recommendations, assess asthma control, generate a risk assessment, and print out asthma action plans and patient prescriptions.

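### The rule for declaring health system costs decreased leaves out non-emergent practitioner visits, although the cost total it judges includes them

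*Protocol article*

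**What the plan says.** All of the conflicting text is in the protocol article, mostly in one paragraph of Economic Analysis.

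- Perspective: "The primary analysis will be from the health care system perspective".
- Quantity: "Total health system costs per child with asthma in the 2 trial arms before and after the intervention will be determined".
- Composition: the total has three parts. Part 1 is implementing the pathway and training the trainers, part 2 is education given by chronic disease management professionals, and part 3 is "those from hospitalizations and emergency department and practitioner visits for asthma". Part 3 does not restrict practitioner visits to emergent ones.
- Verdict: overall costs count as having fallen "if the cost decrease from reduced emergent physician visits, emergency department visits, and hospitalization outweighs the cost increase from pathway implementation and asthma education", with no other item on either side.

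The next paragraph of the section again leaves visits unrestricted: "Costs stemming from health care utilization (drugs, hospitalizations, emergency department, and practitioner visits) will be derived from health administrative data". So does Quantitative Data, which lists "practitioners visits (*Alberta physician/NP claims" among the administrative sources.

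Project Objectives treats the intervention as successful if it produces either cost savings or better quality of life for child and parent. Success leads to a strategy for province-wide spread.

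**The concern.** The verdict sentence claims to judge overall health system costs but uses a narrower set of items than the total just defined. It credits avoided emergent physician visits, emergency department (ED) visits and admissions, and debits the programme. A change in scheduled or other non-emergent practitioner visits for asthma moves the total but cannot move the verdict.

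The qualifier does not look accidental. Background and Overview also writes it when listing utilization aims, so its absence from part 3 reads as a wider category.

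An intervention that shifts care from urgent to planned contacts is the case in which the two would diverge. Cost savings alone can count as success, so the trial could report a saving that its own total does not show, or understate a real one.

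**Working it through.** The documents state no cost figure, so there is none to reproduce. The check sets the rule against the total.

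**Definitions, per child, as the effect of the intervention**

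- S = S_emergent + S_ED + S_hosp, the savings the rule credits.
- I = the added cost of implementation and education (parts 1 and 2; train-the-trainer cost is taken as inside I).
- V = the change in the cost of non-emergent practitioner visits for asthma. It belongs to part 3 and is absent from the rule.

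**Comparison**

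- Rule: decreased if S > I.
- Change in part 3: V − S.
- Change in the three-part total: I + (V − S) = I − S + V. The total falls only if S > I + V.
- False decrease: the rule is met and the total rises when 0 < S − I < V.
- If V < 0, the total falls by more than S − I, so the rule understates the saving. It misses a decrease altogether when V < S − I ≤ 0.

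**Illustration (all costs assumed)**

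Take S_emergent = 10, S_ED = 30 and S_hosp = 40, so S = 80, and I = 60. The rule's margin is 80 − 60 = 20, so it says decreased whatever V is.

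| V | Rule | Total, 60 − 80 + V | Part 3, V − 80 | Practitioner visits, V − 10 |
|---|---|---|---|---|
| −20 | decreased | −40 | −100 | −30 |
| 0 | decreased | −20 | −80 | −10 |
| 20 | decreased | 0 | −60 | +10 |
| 30 | decreased | +10 | −50 | +20 |
| 50 | decreased | +30 | −30 | +40 |
| 80 | decreased | +60 | 0 | +70 |

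The verdict is wrong from any V above 20. Part 3 as a whole is still falling there, and rises only when V exceeds 80.

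**Rough scale of S (assumed ranges)**

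Background and Overview aims for a 20% reduction in ED visits and in hospitalizations; the same is assumed here for emergent visits. Assume per child-year 0.10–0.30 ED visits, 0.01–0.03 admissions and 0.3–0.8 emergent visits. Assume these cost 3–6, 40–80 and 1 times a scheduled visit. Then S in scheduled-visit units is:

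- low: 0.2 × (0.10×3 + 0.01×40 + 0.3×1) = 0.20
- middle: 0.2 × (0.20×4 + 0.02×60 + 0.5×1) = 0.50
- high: 0.2 × (0.30×6 + 0.03×80 + 0.8×1) = 1.00

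Under these inputs S is worth at most about one scheduled visit per child-year, so V would not have to be large to matter. The calculation does not set I, so it does not show that the rule would be met.

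**The case against.** **The total will be computed anyway.** True. It is planned by arm, before and after, with all practitioner visits in part 3, so the net change can be recovered and no data are lost. But the rule, not that total, is what the article uses to define a decrease.

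**The sentence is shorthand, or implementation cost covers visits that the pathway generates.** This is possible. However, the article's own split puts practitioner visits in part 3 and implementation in part 1, and the rule names only some of the part 3 items. If it is shorthand, aligning it takes one sentence.

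**Nothing shows that scheduled visits will rise.** This stands. The electronic tool lets practitioners "classify patient’s disease phenotype to generate therapeutic recommendations, assess asthma control, generate a risk assessment, and print out asthma action plans", which may happen within visits that would have taken place anyway, and education by chronic disease management staff is costed in part 2. A reader might infer that the rule is biased toward finding savings. The documents do not support that, because better control could also reduce non-emergent visits.

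**The stakes are limited.** This also stands in part. Project Objectives does not cite this rule when it speaks of cost savings, success leads to developing a strategy, and Economic Analysis says cost effects will be weighed alongside outcomes, including quality of life.

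**Conclusion.** The mismatch is real and rests on the text alone: non-emergent practitioner visits for asthma are inside the total and outside the rule that judges it. The error in the rule's margin equals V. The verdict is falsely favourable when 0 < S − I < V, and the saving is understated when V < 0. The sign and size of V are not documented, so neither the direction nor the probability of a wrong verdict can be stated.

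Two stronger readings are tempting and should not be adopted:

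- That fewer emergent events with more scheduled visits means part 3 itself has risen. That needs V > S, a much stricter condition than the one that reverses the verdict.
- That one extra scheduled visit per child-year cancels the saving while the rule still reports a decrease. Apart from the 20% goal for ED visits and hospitalizations, its inputs are assumed. It also says nothing about I, and with a modest programme cost the rule might report no decrease at all.

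The point affects a secondary economic conclusion, not the primary outcome. It is still worth correcting, because that conclusion can count as success on its own.

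**What to change.** Replace the verdict sentence in Economic Analysis with one along these lines:

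> The effect on health system cost will be judged by the between-arm difference in change, from baseline to follow-up, in total health system cost per child. The total will include every practitioner visit for asthma, scheduled or emergent, and the difference will be reported with its 95% CI.

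State in advance how the interval enters the verdict. If a point estimate below zero were enough, savings would be declared about half the time when there is no true effect. The interval should allow for clustering by practice. Show scheduled and emergent visits as separate lines so that any substitution is visible.

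While editing, also settle whether drug costs belong in the total. The utilization costs list them, but neither the three parts nor the rule does. That is a separate gap and is not counted in this point.

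The cost is a sentence or two and one extra table line. The practitioner claims are already to be obtained, so no new data are needed beyond a working definition that separates emergent from scheduled visits. The downside is that the cost result may look less favourable.
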